## Abstract

**Background:**

For most patients with pregnancy hyperglycemia, treatment includes lifestyle behavioral counseling for a healthy diet and physical activity (PA). Outside of pregnancy, emerging evidence suggests that the *timing* of PA (e.g., in the morning vs. evening) may modify its glucose-lowering effects. PA is an evidence-based, non-pharmacological strategy for managing glucose levels, and recommendations for PA *timing* could improve glucose levels in individuals with pregnancy hyperglycemia.

**Objective:**

To describe the rationale and protocol of the Time to Move Randomized Crossover Trial, which evaluates the effects of morning vs. evening PA on glucose levels across the 24-hour cycle.

**Methods:**

The eligibility criteria include singleton pregnancies in patients aged 18–40 years, identified as having gestational glucose intolerance [(GGI), a non-fasted, 50-g glucose challenge test, 1-hour value ≥130 mg/dl] or gestational diabetes mellitus [(GDM), by the one- or two-step procedure, at ≥24 weeks]. Participants who provide consent are randomized to first perform either morning PA (between 5 a.m. and 9 a.m., within 30 min–40 min of starting breakfast) or evening PA (between 4 p.m. and 8 p.m., within 30 min–40 min of starting dinner). All PA episodes consist of 30 min of moderate-intensity walking or stepping. Participants ultimately contribute 2 days in each of the three treatment conditions: morning PA, evening PA, and no PA, with one washout day between treatment conditions. Timestamped glucose measurements are obtained using Dexcom G6 or G7 continuous glucose monitors (CGM). The primary analysis will be intention-to-treat; per-protocol associations will also be explored. PA adherence is assessed using ActiGraph PA monitoring devices (i.e., the CentrePoint Insight Watch, worn on the non-dominant wrist), which provide continuous timestamped estimates of movement. Participants upload photos (i.e., in real time) of all foods and beverages consumed throughout the study period, and the timestamps of these photos are used to identify postprandial periods. One 24-hour dietary recall, aided by photo uploads, is also completed for each treatment condition.

**Conclusions:**

The Time to Move Randomized Crossover Trial addresses the gap in scientific knowledge regarding whether the *timing* of PA may be leveraged to maximize glucose control in individuals with pregnancy hyperglycemia.

**Clinical trial registration:**

## Background

1

Gestational diabetes mellitus (GDM), or hyperglycemia first recognized during pregnancy, is diagnosed in up to 9% of pregnancies in the United States and has been increasing in recent years (1, 2). GDM confers an increased risk of adverse pregnancy outcomes, including premature delivery, induction of labor, Caesarean delivery, and delivery of a large-for-gestational-age neonate, as well as heightened risks for future cardiometabolic disease in the mother and obesity in the child. Similar risks have been reported in individuals with gestational glucose intolerance (GGI), who have abnormal screening test results for GDM without meeting the diagnostic criteria for GDM. Individuals with GGI are at an increased risk of delivering a large-for-gestational-age (LGA) neonate (3) and developing diabetes later in life (4).

For most patients with pregnancy hyperglycemia, treatment includes medical nutrition therapy for a healthy diet, physical activity (PA), and gestational weight gain within the ranges recommended for the patient’s pre-pregnancy body mass index (BMI) category, per the 2009 Institute of Medicine [IOM; now the National Academy of Medicine (2, 5)]. The recommended caloric intake and diet composition for individuals with pregnancy hyperglycemia do not differ from those for pregnant individuals without the condition (2, 5). They include a minimum of 175 g of carbohydrate (approximately 35% of a 2,000-calorie diet), a minimum of 71 g of protein, and 28 g of fiber (6–8). Behavioral counseling for a healthy diet, or Medical Nutrition Therapy (MNT) in a clinical setting, typically includes developing an individualized nutrition plan in conjunction with a Registered Dietitian Nutritionist (RDN) familiar with the management of GDM (2). Guidelines vary, but most recommend the distribution of carbohydrate intake into three small snacks (i.e., each 5%–10% of total carbohydrate intake) and three main meals [i.e., breakfast (10%–15% of total carbohydrate), lunch (20%–30%), and dinner (30%–40%)] per day (9). Lower carbohydrate intake is recommended at breakfast versus lunch and dinner due to the morning peak of cortisol secretion, which drives, at least in part, the high blood glucose values observed after breakfast (9) among individuals with pregnancy hyperglycemia.

Patients with pregnancy hyperglycemia are given the same standard recommendation for PA as healthy pregnant and non-pregnant adults: to achieve 150 min of moderate-intensity aerobic activity per week, preferably spread throughout the week (2, 5). A systematic review demonstrated improvements in glucose outcomes with exercise interventions (with exercise defined as PA that is intentionally performed for health or wellness) in pregnancy hyperglycemia; however, the review noted that heterogeneity in the types of activity (i.e., aerobic, resistance, or both), as well as the duration (i.e., 20 min–50 min per day) and frequency (i.e., 2–7 days per week) of activity, resulted in insufficient evidence to allow for recommending a specific type of program (2, 10). Walking is the most frequently reported type of PA among pregnant individuals (11). In pregnancies with GDM, postprandial walking (12), including light-intensity walking (13), effectively manages postprandial glucose excursions compared to no postprandial activity. More PA, specifically more steps accumulated in a day, is also associated with improved blood glucose concentrations in GDM (14). However, the distribution of the 30 min of walking, that is, whether to divide it into 10-minute episodes performed after each major meal or done continuously for a single 30-minute, postprandial episode, does not appear to differentially affect glucose outcomes (15, 16).

Meeting the PA recommendation through daily PA or participating in PA on most days of the week is recommended for non-pregnant adults with diabetes (17); however, no guidance on the *timing* of PA (e.g., morning or evening) has been provided. Outside pregnancy, emerging evidence suggests that the timing of PA may modify its impact on metabolic health. In a cross-sectional study of over 60,000 non-pregnant German adults, afternoon and evening activities provided greater metabolic health benefits than morning activity (18). PA recommendations for individuals with pregnancy hyperglycemia currently provide no guidance on the *timing* of PA (2, 5), although high blood glucose values earlier in the day have been reported in this population (9).

The timing of PA may also be leveraged to optimize glucose management and metabolic health in individuals with pregnancy hyperglycemia (19, 20). Behaviorally, performing PA at the same time each day helps with adherence by making PA planning easier and less complex; many behavioral PA interventions encourage action plans for PA, including plans for when PA will be performed (19, 20). PA timing may impact metabolism by affecting appetite, eating behaviors, and sleep (21, 22), in addition to physiological processes beyond PA-related increases in energy expenditure (19, 20), including greater fat oxidation (23) and various circadian influences [e.g., melatonin rhythms that influence sleep/wake timing (24–26)].

A scarcity of time to perform PA is a commonly cited barrier among non-pregnant and pregnant individuals alike (27); thus, in terms of adherence to PA, any time of day is technically the ‘right time’ for PA in this population. However, in the era of advanced technology and precision medicine, there is growing interest in leveraging rhythms, routines, and 24-hour behaviors to maximize metabolic health (28). PA is an evidence-based, non-pharmacological strategy for managing glucose levels. Following an acute bout of PA, glucose uptake remains elevated for approximately 2 h by insulin-independent mechanisms and for up to 48 h by insulin-dependent mechanisms, particularly if PA is prolonged (29).

This manuscript provides an overview of the Time to Move Randomized Crossover Trial. The Trial’s objective is to compare 30 min of moderate-intensity walking or stepping (30) (i.e., walking in place) under free living conditions, performed either in the morning (i.e., within 30 min to 40 min of starting breakfast) or in the evening (i.e., within 30 min to 40 min of starting after dinner). Previous research by our group suggests that stepping is an acceptable alternative to walking, and given the commonly cited barrier of a lack of time for PA, it may be advantageous in that it can be accomplished while performing other activities that are already part of the everyday routine (30). The primary outcomes include glucose metrics across the 24-hour cycle, assessed using continuous glucose monitors (CGM). We hypothesize that morning PA would improve daytime (6 a.m.–11:59 p.m.) glucose levels, as well as post-breakfast and post-lunch glucose levels, while evening PA will improve post-dinner, nighttime (12 a.m.–5:59 a.m.) (31), and pre-breakfast glucose levels, and thus ultimately improve 24-hour glucose levels. Secondary outcomes include mood during and sleep following bouts of PA. The timing of PA could potentially be leveraged to improve glucose management in this population, thereby leading to improved outcomes for mothers and children.

## Methods

2

The Time to Move Randomized Crossover Trial is registered at ClinicalTrials.gov (ID# NCT06125704; first submitted on 30 October 2023, and first posted on 9 November 2023) and approved and monitored by the University of Tennessee Health Science Center College of Medicine, Knoxville, Institutional Review Board (Study #5079). To the extent possible, this methods paper follows the SPIRIT 2025 statement’s updated guidelines for protocols of randomized trials (32).

### Study setting

2.1

The Time to Move study is being conducted at the University of Tennessee Medical Center (UTMC) in Knoxville, Tennessee. The UTMC serves as a referral center for a 28-county region in East Tennessee, Kentucky, Virginia, and North Carolina. In 2023, UTMC had 4,606 patient deliveries, of which 3.4% were GGI and 11.8% were GDM; 72.8% were White (non-Hispanic), 17.1% Hispanic, and 6.8% Black (non-Hispanic), and over half (57.6%) had public insurance (i.e., TennCare, the state of Tennessee’s Medicaid program). Pregnant individuals are screened for GDM using a 50-gram 1-hour oral glucose tolerance test (OGTT); if abnormal at the threshold of ≥130 mg/dl, it is followed by a 100-gram, 3-hour OGTT. GDM is diagnosed if two or more of the four plasma glucose values obtained during the 100-gram, 3-hour OGTT meet or exceed the Carpenter and Coustan thresholds (2, 33).

### Eligibility and recruitment

2.2

The Time to Move study aims to randomize and follow 39 participants receiving prenatal care at UTMC. Recruitment began on 1 December 2023. The eligibility criteria include singleton, viable pregnancy with low suspicion of clinically significant abnormality or aneuploidy; 18–40 years of age (at the time of recruitment); comfortable communicating with study staff in English and completing study surveys in English (i.e., no translator needed); willingness to use a personal cell phone for study activities (e.g., complete surveys and telephone interviews); and GGI or GDM status. GGI is defined as a plasma glucose ≥130 mg/dL on the 50-g, 1-hour Glucose Challenge Test (GCT; non-fasted). Individuals with GGI undergo a 100-gram, 3-hour OGTT, performed after an overnight fast, at ≥24 weeks gestation, and GDM is diagnosed if at least two of the four plasma glucose values on the OGTT meet or exceed the following thresholds: 95 mg/dL for fasting, 180 mg/dL for 1-hour, 155 mg/dL for 2-hour, and 140 mg/dl for the 3-hour timepoint. Individuals with GDM diagnosed by the one-step procedure are also eligible [i.e., only a 75-g OGTT performed after an overnight fast, at ≥24 weeks gestation, with at least one plasma glucose value meeting or exceeding the thresholds of 92 mg/dL for fasting, 180 mg/dL for 1-hour, and 153 mg/dL for the 2-hour timepoint]. Individuals with GDM identified by a 50-g, 1-hour GCT plasma glucose ≥180 mg/dL are also eligible.

The exclusion criteria are as follows: physician determination that PA, particularly walking, should be limited in the current pregnancy; a prior diagnosis of diabetes, outside of pregnancy; current use of daily medications known to alter insulin resistance and/or metabolic profiles (e.g., insulin, metformin, corticosteroids, and anti-psychotics); current use of medication for polycystic ovarian syndrome (PCOS); and conditions that interfere with one’s ability to follow a strict, time-based study protocol (e.g., psychiatric illness). Individuals working night shifts or with circumstances (e.g., lifestyle factors, religious observance) that precluded their ability to follow a strict, time-based study protocol are also excluded.

Potentially eligible patients are identified by clinic and study staff, who review the electronic medical records to conduct a preliminary eligibility assessment. The study staff then briefly explain the study, either in-person (i.e., meeting the patient at their OGTT) or by phone or text message, to assess interest. Potentially eligible patients, per the preliminary assessment, are then reviewed by an MD for the final determination of eligibility.

### Consent and randomization

2.3

Potential participants are invited to schedule an Information Session (remote or in-person) to learn more about the study. They are emailed a link to the study consent form and asked to review it ahead of the Information Session. The consent and all study procedures are reviewed at the Information Session; time is allotted to answer questions prior to signing the consent.

Participants are then randomized in SAS to either morning PA followed by evening PA or evening PA followed by morning PA (**Figure 1**, [*18*]); the crossover design allows each participant to serve as their own control. Participants are instructed to perform no PA for health or wellness on the day of the Study Visit (i.e., day 0) and on days 2, 5, and 7, which served as wash-out days. PA (described in greater detail in the following section) is performed on days 3 and 4 and again on days 8 and 9. No PA for health or wellness is performed on days 1 and 6, thereby providing two full days’ (i.e., 48 h) worth of data under each treatment condition (i.e., morning PA, evening PA, and no PA).

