### Conditions

2.4

For PA, participants are instructed to perform 30 min of moderate-intensity walking or stepping (i.e., walking in place or around a small area) (34) following the respective meal. Moderate-intensity PA is described as activities during which you can comfortably talk but not sing. Moderate-intensity walking or stepping is described as a cadence of approximately 100 steps per minute. Well-known songs at 100 beats per minute, such as the Bee Gee’s *Stayin Alive* and Beyonce’s *Crazy in Love*, are recommended to help participants walk or step at 100 steps per minute (35). On days they are assigned morning PA, participants are instructed to walk or step between 5 a.m. and 9 a.m. and to begin their PA 30 min–40 min after the start of their breakfast. On days they are assigned evening PA, they are to walk or step between 4 p.m. and 8 p.m. and begin 30 min–40 min after the start of their dinner. Adherence to PA is defined as completing at least 80% of the assigned PA during the assigned window (i.e., 24 min or more of the continuous walk/run activity type, as detected by the device (see Section *Device-assessed physical activity*), during the assigned timeframe). Participants are instructed to not perform any additional PA intentionally for health or wellness outside of the assigned (by day and time range) walking or stepping for the duration of the study.

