#### Glucose outcomes

2.5.1

Initially, the participants wore blinded Dexcom G6 CGMs. On 9 December 2024, the IRB approved a modification for unblinded Dexcom G7 CGMs due to the phasing out of the G6. The CGM is placed on the back of the upper arm. The participant is asked to use the side on which they were least likely to sleep for CGM placement (i.e., to avoid compression lows). All CGM data are accessed via Dexcom’s Clarity system.

Glucose outcomes include the mean, area under the curve (AUC), and coefficient of variation (CV) for 24-hour glucose, daytime glucose, and nighttime glucose; percentage of time in range (TIR), percentage of time above range (TAR), and percentage time below range (TBR) were added after the trial was underway. For 24-hour glucose, the start times will vary by treatment; specifically, 24-hour summaries are anchored (begin at) at 4 a.m. for morning PA days, 3 p.m. for evening PA days, and midnight on no PA days. The daytime window is defined as 6 a.m. to 11:59 p.m., and the nighttime window as 12 a.m. to 5:59 a.m (31). Glucose outcomes also include the mean, AUC, and CV for the pre-breakfast (calculated for the 120 min prior to the start of breakfast) and all post-meal periods (calculated for the 120 min after the start of breakfast, lunch, and dinner). The identification of the *time* of the start of breakfast, lunch, and dinner is described in Section *Dietary intake and meal times*.

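### The second no-PA control day (day 6) opens 28 to 42.5 h after the last bout, within the up-to-48-h after-effect the protocol cites, while day 7, PA-free and beyond 48 h, is set aside as washout

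*Protocol article*

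**What the plan says.** All references are to the protocol article.

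- **Schedule (Consent and randomization).** PA "is performed on days 3 and 4 and again on days 8 and 9". The no-PA condition is supplied by two other days: "No PA for health or wellness is performed on days 1 and 6". The PA-free days 0, 2, 5 and 7 supply no condition; of these the article writes "on days 2, 5, and 7, which served as wash-out days".
- **Washout rule (Abstract, Methods).** Each participant gives two days per condition "with one washout day between treatment conditions".
- **Clock windows (Conditions).** For morning PA "participants are instructed to walk or step between 5 a.m. and 9 a.m"; for evening PA "they are to walk or step between 4 p.m. and 8 p.m". Each bout lasts 30 min.
- **Summary windows (Glucose outcomes).** The 24-hour summary starts at 4 a.m. on morning PA days, "3 p.m. for evening PA days, and midnight on no PA days". Nighttime runs from midnight to 5:59 a.m.
- **Duration of the effect (Background).** After an acute bout, glucose uptake stays raised for about 2 h by insulin-independent mechanisms and "for up to 48 h by insulin-dependent mechanisms, particularly if PA is prolonged".

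The article gives no reason for a washout day after a no-PA day.

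**The concern.** A washout belongs after exposure. Between the two PA blocks there are three PA-free days: 5, 6 and 7. The plan analyses the middle one as control and sets aside the last, although the last is 24 h further from the exercise and follows a day with nothing to wash out. On the protocol's own statement about duration, the day used may carry some residual effect and the day set aside should not.

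Day 6 is half of the control data. Residual glucose lowering on it would bring the no-PA mean closer to the PA means and pull PA-versus-no-PA contrasts toward the null. Exposure also depends on the randomized sequence, because an evening bout on day 4 ends later than a morning one. The night window is the most exposed part of day 6, and the Background section hypothesizes that evening PA improves nighttime and pre-breakfast glucose. The no-PA condition enters the three-condition comparison in Statistical analyses.

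**Working it through.** The plan states no figure for residual carry-over. Its one computed figure, power 0.89 at 36 participants, does reproduce: f = √(3 × 0.15/0.85) = 0.728, and a noncentral F with 2 and 70 degrees of freedom, noncentrality f² × 36 and alpha 0.007 gives 0.885 (0.888 with f rounded to 0.73). It is not used below.

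**1. Hours from the last bout to the control day.** Inputs: last first-period bout on day 4; bout length 30 min; windows 5 to 9 a.m. and 4 to 8 p.m.; the no-PA day opens at midnight. The earliest bout end is the window opening plus 30 min; the latest is the window close.

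| First condition | Bout ends, day 4 | To start of day 6 | Day 6 within 48 h | Share of 24 h | To start of day 7 |
|---|---|---|---|---|---|
| Evening PA | 16:30 to 20:00 | 28 to 31.5 h | 16.5 to 20 h | 69 to 83% | 52 to 55.5 h |
| Morning PA | 5:30 to 9:00 | 39 to 42.5 h | 5.5 to 9 h | 23 to 38% | 63 to 66.5 h |

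Example: 20:00 on day 4 to 00:00 on day 6 is 4 + 24 = 28 h, and 48 − 28 = 20 h of day 6 remain inside the limit. The shares are shares of clock time, not of effect.

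**2. Night window (midnight to 5:59 a.m. on day 6).** Evening first: all 6 h lie within 48 h. Morning first: 5.5 to 6 of 6 h.

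**3. Spacing of the two PA blocks.** From the 8 p.m. close on day 4 to the 5 a.m. opening on day 8 is 81 h. From the 9 a.m. close to the 4 p.m. opening is 103 h. Both exceed 48 h.

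**4. Effect on the contrast.** Let c be the mean residual effect on day 6 as a fraction of the mean PA-day effect. Day 6 is one of two control days, so the PA-versus-no-PA contrast shrinks by c/2. The documents give no value for c. The values below are assumptions.

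*Linear decay.* The effect is 1 − t/48, with t the hours since the latest bout.
- Day-6 mean = (48 − t₀)²/(2 × 48 × 24), with t₀ the hours at midnight. Evening first: 0.174 (t₀ = 28) to 0.118 (t₀ = 31.5). Morning first: 0.035 (t₀ = 39) to 0.013 (t₀ = 42.5).
- PA-day mean, averaged over the two days of a block. A bout at the end of its window leaves 19 h in the first day's 24-hour summary: (19 − 19²/96)/24 = 0.635. The second day's summary covers a full 24 h cycle: (24 − 24²/96)/24 = 0.75. Average 0.69. For the earliest bout, 22.5 h remain on the first day and the average is 0.73.
- Evening first: c = 0.118/0.73 = 16% to 0.174/0.69 = 25%. Morning first: c = 0.013/0.73 = 2% to 0.035/0.69 = 5%.
- Averaged over equal sequences: c = 9 to 15%, so c/2 = 4.5 to 7.5%. If the effects of the two bouts add up instead, the PA-day means rise to 0.81 to 0.86 and c/2 is 3.8 to 6.4%. Together this is roughly 4 to 8%.

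*No decay at all until hour 48* (limiting case, latest-bout convention). Evening first: c = 16.5/23.25 = 71% to 20/21.5 = 93%. Morning first: c = 5.5/23.25 = 24% to 9/21.5 = 42%. Averaged: 47 to 67%, so c/2 = 24 to 34%. If the effects of the two bouts add up, c/2 is 16 to 23%.

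**The case against.** **The 48 h is a ceiling.** The Background section ties it particularly to prolonged PA, and these bouts are 30 min of walking or stepping. The effect may be gone well before day 6. This stands: the schedule makes carry-over possible and does not show it.

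**The main comparison is safe.** The objective is morning versus evening PA. The two blocks are at least 81 h apart, and both PA conditions are compared with the same control mean, so a shift in that mean cancels. This also stands and confines the point to the no-PA contrasts.

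**The plan keeps its own rule.** Day 5 is a full PA-free day between day 4 and day 6. True, but one calendar day is shorter than the period the article cites, and the same rule spends day 7 where there is no exercise to clear.

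Two stronger readings are tempting and not supported:

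- A reader might infer that the washout is really only 9 h, because the evening-PA summary for day 4 runs to 3 p.m. on day 5. That mixes a measurement window with washout. Washout runs from the end of the bout, and that gap is at least 28 h.
- A reader might take 25 to 50% of the effect as persisting on day 6 and infer an attenuation of 12.5 to 25%. The documents give no such fraction, and one value cannot serve both sequences: after morning PA, even an effect with no decay until hour 48 gives c of at most 42%.

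**Conclusion.** The point holds as a mismatch between the schedule and the protocol's own statement of how long the effect can last. The clock arithmetic follows directly from the stated windows: in both sequences day 6 opens inside 48 h, and all of day 7 lies outside it. That day 7 goes unanalysed is inferred from its washout label and from only days 1 and 6 being counted as no-PA data.

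The direction of any bias is clear: toward the null for PA versus no PA, and stronger in evening-first participants. Its size is unknown. Roughly 4 to 8% attenuation follows if the effect decays linearly to zero at 48 h, if morning and evening effects are equal and if the sequences are balanced. Slower decay gives more, faster decay less, and none is possible. The morning-versus-evening result is not at risk. This is a cheap improvement worth making, not a flaw that invalidates the trial.

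**What to change.** Before unblinding, specify day 7 as the second no-PA analysis day, treat days 5 and 6 as washout, and keep day 6 as a sensitivity analysis. At minimum, add a sensitivity analysis with day 7 in place of day 6. For participants still to enrol, draw the no-PA dietary recall from day 1 or day 7. Reconcile the washout wording in the Abstract and in Consent and randomization with the duration given in the Background section.

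Participants do nothing different, since days 5 to 7 are already PA-free. Meal photos are uploaded throughout the study period, with the daily meal-time survey as backup. Continuous glucose data for day 7 should exist too, assuming the sensor is worn without a break. A midnight-to-midnight day 7 ends before the 4 a.m. start of the day-8 morning summary, so no windows overlap. Investigators see results only under coded treatment labels until the Results section is drafted, so the change can be made without knowledge of the effects.

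Costs and limits:

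- The recall day is picked at random from the two days of a condition. About half of those already followed therefore have their no-PA recall on day 6, and their diet covariate would come from a day outside the primary analysis.
- Day 7 would be followed directly by the PA on day 8, so the rule of one washout day between every pair of conditions must be reworded. Nothing is lost, as no exercise precedes day 8 within 48 h.
- Day 1 is unchanged. Its only stated PA-free lead-in is day 0, so the change does not guarantee 48 h without PA before every control day.
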